**Efficacy study of electroacupuncture for women with pure stress urinary incontinence: study protocol for a pilot randomized placebo controlled trial**

**Background**

Acupuncture is a potential conservative therapy for women with stress urinary incontinence (SUI). There are limited evidences to support its effectiveness due to poor quality of existing studies.

**Objective**

To explore the efficacy and safety of electroacupuncture (EA) for women with pure SUI.

**Methods**

**Study design**

This is a randomized, placebo-controlled study comparing EA with sham EA. Eighty women with pure SUI will be recruited from department of acupuncture and moxibustion of Guang’anmen hospital of China Academy of Chinese Medical Sciences (CACMS), Beijing, China. Participants will be randomly assigned to EA group or sham EA group by central randomization with a 1:1 ratio. The central randomization system was performed by the Clinical Evaluation Center of CACMS in Beijing. Random number and group assignment will be offered by telephone, mobile phone, or website from the Clinical Evaluation Center. In this study, participants, outcome assessors and statisticians are blinded to treatment allocation. This study was registered on ClinicalTrials.gov (Identifier: NCT02445573).

**Ethics**

The study was conducted in accordance with the Declaration of Helsinki, and the protocol was reviewed and approved by the Ethics Committee of Guang’anmen hospital of China Academy of Chinese Medical Sciences (CACMS). Written informed consent will be obtained from each subject before patients entering the trial.

**Participants**

The trial is planned to recruit 80 women with pure SUI. Potential participants were guided to finish the laboratory examinations (urine routine, urine flow rate and the residual urine), fill out 72-hour bladder diary and ICIQ-SF, and take 1 hour pad test by research assistants during 1-week baseline assessment to determine eligibility.

Diagnostic criteria are as follows:

1. involuntary urine leakage on effort, exertion, sneezing or coughing, which stopped when the stress ends;
2. visible involuntary leakage from the urethra synchronous with increased abdominal pressure;
3. a pad weight gain >1 g in 1-hour pad test.

Inclusion criteria are as follows:

1. 40 to 75 years of age;
2. meet diagnostic criteria;
3. without symptoms of urinary frequency and urgency.

Exclusion criteria are as follows:

1. met any of the following criteria: other type of UI (urge, mixed, or overflow UI, etc);
2. symptomatic urinary tract infection; ever received UI or pelvic surgery; a severity of pelvic organ prolapse ≥ degree 2;
3. residual urinary volume >30 ml;
4. maximum flow rate ≤ 20 ml/s;
5. limited in walking, stairs climbing and running; receiving specialized treatment for SUI, or taking medicine affecting bladder function;
6. serious cardiovascular, cerebral, liver, kidney, or psychiatric disease, diabetes, multiple system atrophy, injury of cauda equina, or myeleterosis;
7. being pregnant or breastfeeding;
8. with cardiac pacemaker, metal allergy or severe needle phobia;
9. unlike to give written formed consent.

**Interventions**

Acupuncture operation will be performed by registered acupuncturists who have more than two years’ experience.

Disposable acupuncture needle (size 0.30×75 mm), pragmatic placebo needle (size 0.30×25 mm) and SDZ-V EA apparatus (all were Hwato Brand, Suzhou Medical Appliance Factory, Suzhou, China) were used in this trial.

***EA group***

In EA group, acupoints of bilateral BL33 (Zhongliao) and BL35 (Huiyang) were used. BL33 is on the third posterior sacral foremen. BL35 is 0.5 cun lateral to the tip of the coccyx. When acupuncturing, adhesive pads were first pasted on acupoints after sterilization in either group. In EA group, participants were needled at bilateral BL33 at an angle of 30 to 45 degree inward and downward, and at bilateral BL35 slightly toward upside and outside, to a depth of 50 to 60 mm using acupuncture needles of size 0.30×75 mm. Needles were then lifted, thrusted and twirled evenly for 3 times to achieve deqi (also termed as needle sensation, is a composite of unique sensations interpreted as the flow of qi induced by acupuncture, and is believed to be essential for a good clinical effect). To implement a standardized operation among different participants, no more needle manipulation would be performed even if the required manipulation failed to achieve deqi. Paired electrodes of EA apparatus were attached transversely to bilateral BL33 and BL35 (using real electrodes) respectively, with a continuous wave of 50 Hz and a current intensity of 1-5 mA for 30 min. Participants were treated with EA 3 sessions a week on alternate days for 6 successive weeks.

***sham EA group***

In sham EA group, participants were needled at sham BL33 and sham BL35, which were about 20 mm lateral to BL33 and BL35, respectively, with blunt needle tips piercing adhesive pads and not piercing the surface of the skin, using placebo needles of size 0.30×25 mm. Needles were then lifted, thrusted and twirled evenly for 3 times to achieve deqi. Paired electrodes of EA apparatus were attached transversely to bilateral sham BL33 and sham BL35 (using sham electrodes) respectively with same parameters and treatment courses.

To improve the effect of blindness, participants were informed that this trial was to compare the effects of two EA methods for pure SUI. One was traditional EA using conventional acupoints and electric current, and the other was non-traditional EA by needling on non-traditional acupoints with a weak electric current. The inform was approved by our ethics committee. Participants were discouraged from any other specialized treatments of SUI, mainly referring to SUI medications such as duloxetine, PFMT, feedback therapy, electrical or magnetic stimulation via pelvic floor, vagina or anus, and transcutaneous electrical nerve stimulation to pelvic floor. During the treatment period, if a participant was in her menstrual cycle, the treatment was postponed until the cycle ended. The length of delay was not included in the treatment period. It took 32 weeks in total for a patient to complete the trial: 1 week’s screening, 1 week’s baseline assessment, 6 weeks’ treatment, and 24 weeks’ follow up.

**Outcome measures**

**Primary outcome:**

Change from baseline of urine leakage after 6 weeks measured by 1-hour pad test.

**Second outcomes:**

1. Change from baseline of the mean 72-hour incontinence episode frequency (IEF) during weeks 1-6, weeks 15-18 and weeks 27-30;
2. Change from baseline of the total ICIQ-SF scores at weeks 6, 18 and 30;
3. Patient self-evaluation of therapeutic effect at weeks 6, 18 and 30.

Data of IEF was from 72-hour bladder diary. The bladder diary was recorded in detail the time and frequency of UI, activity that occurred at the time of leak, and the type and volume of liquid intake. In case that a participant was in her menstrual cycle or suffering from severe cough during an assessment week, she needed not to record the bladder diary until the end of cycle or the recovery of cough.

**Safety Monitoring**

We only recorded and evaluated all the serious adverse events (SAEs) and the AEs related with EA, including local pain from needling, slight bleeding or hematoma, persistent pain after EA, discomfort after EA (remaining uncomfortable needle sensation, fatigue, etc), stuck needle, fainting during acupuncture, broken needle, and infection. Participants were instructed to report AEs throughout the study by contacting the outcome assessor at each visit or by telephone.

Pain or discomfort caused by acupuncture (if there was) was assessed using a 10-point visual analogue scale (VAS, 0 indicates no pain/discomfort, and 10 indicates the severest pain/discomfort). Acupuncture pain with a spontaneously remission within 30 min after acupuncture was not regarded as AE. Other common AEs which were obviously not related to acupuncture (like catching cold) were neglected. The rate of AEs were calculated using data from patients with ≥1 AEs.

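### Relatedness to EA is an entry filter for non-serious adverse events, so the all-cause comparison of these events between EA and sham is lost at data capture

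*Protocol*

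**What the plan says.** The Objective section gives safety equal standing with efficacy: "To explore the efficacy and safety of electroacupuncture (EA) for women with pure SUI". Safety Monitoring then sets the recording rule: "We only recorded and evaluated all the serious adverse events (SAEs) and the AEs related with EA". A list of needling and stimulation events follows, offered as examples. A later sentence disposes of the remainder: "Other common AEs which were obviously not related to acupuncture (like catching cold) were neglected".

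The same section defines a threshold for pain, "Acupuncture pain with a spontaneously remission within 30 min after acupuncture was not regarded as AE", and a reporting route, "Participants were instructed to report AEs throughout the study by contacting the outcome assessor at each visit or by telephone". Under Study design, "participants, outcome assessors and statisticians are blinded to treatment allocation"; the acupuncturists are not in that list. The section names no one as judge of relatedness and gives no criteria for it. On summary it says only "The rate of AEs were calculated using data from patients with ≥1 AEs".

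**The concern.** In a 1:1 randomised trial with a sham arm, whether EA causes an event is best learned by comparing how often it occurs in each arm. That requires events to be recorded first and attributed afterwards. Here attribution comes first. A non-serious event that nobody connects with EA leaves no trace in either arm, so the comparison that could have shown the connection is never made.

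The events most exposed are the doubtful and the unexpected. Foreseen needling events are recognised anyway; an unforeseen one depends on an individual judgement for which the protocol states no rule. An analysis plan cannot repair this, because the unrecorded events are not there to analyse or re-review.

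**Working it through.** **The two sentences side by side.** The recording sentence keeps serious events and non-serious events that are related. The disposal sentence drops common events that are obviously unrelated. Between them lie non-serious events of uncertain cause. The disposal sentence does not reach them, but the word only in the recording sentence shuts them out. Their handling is therefore either exclusion or undefined. The 30-minute pain rule differs in kind: it is an explicit threshold that anyone can apply in the same way.

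**Inputs.** Sample Size and Statistical Analysis gives 40 patients per group. The protocol states no adverse event rate and no calculation for safety, so there is no figure of its own to reproduce on this point. All rates and kept fractions below are assumptions, with at most one such event per patient.

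**Formulas.** Recorded rate = true rate × fraction of events judged related. Approximate power for a two-sided 5% comparison of proportions, with n = 40 per arm and p̄ the mean of the two rates: Φ{ [|p1 − p0| − 1.96·√(2p̄(1 − p̄)/n)] / √([p1(1 − p1) + p0(1 − p0)]/n) }.

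**Results (EA vs sham).**
- *No filter.* True rates 30% vs 10%, or 12 vs 4 patients. Power = Φ[(0.20 − 1.96 × 0.0894)/0.0866] = Φ(0.285) = 61%.
- *Same filter in both arms, half kept.* 0.30 × 0.5 = 15% and 0.10 × 0.5 = 5%, or 6 vs 2 patients. The ratio stays at 3, but the difference halves from 20 to 10 points. Power = Φ[(0.10 − 1.96 × 0.0671)/0.0661] = Φ(−0.476) = 32%.
- *Different filter, equal true rates of 30%.* With 80% kept in EA and 40% in sham: 0.30 × 0.8 = 24% and 0.30 × 0.4 = 12%, a false difference of 12 points. Reversing the fractions gives 12% and 24%.
- *Different filter, true rates 30% vs 10%.* With 40% kept in EA and 80% in sham: 12% and 8%. A true difference of 20 points shrinks to 4, and power is about 9%.
- *Worst case.* An event in 20% of EA and 5% of sham patients is 0.20 × 40 = 8 vs 0.05 × 40 = 2 cases. If all 10 are dismissed, the report shows 0 vs 0.

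A filter applied alike in both arms dilutes a difference; one that differs by arm can also create or hide one. Neither could be detected afterwards.

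**The case against.** The strongest reply is that the rule is narrower than it first appears. The list of related events is open-ended and includes pain, discomfort, fatigue and infection, so an unlisted symptom can be recorded if someone thinks it related. A new pelvic or bladder symptom after sacral needling is hardly an obviously unrelated one. All serious events are kept. The trial is a pilot that sets out to explore safety, and no dedicated safety test is written; only the general rule for categorical variables would apply. All of this stands and limits the point. It does not say who decides, by what criteria, or what happens to doubtful events.

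Three stronger readings are tempting but not supported.

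- *The safety objective cannot be met at all.* Serious events, and a descriptive rate of procedure-related events, survive the filter. What is lost is the all-cause comparison of non-serious events.
- *The filtering depends on arm.* Reports go to an outcome assessor who is blinded, and nothing says that someone who knows the allocation decides. Silence on who decides is a gap, not evidence of bias. Nor is it a recording bias that the sham, with "blunt needle tips piercing adhesive pads and not piercing the surface of the skin", produces few hematomas or stuck needles: that is a true difference between the procedures.
- *The adverse event rate has the wrong denominator.* Read literally, "The rate of AEs were calculated using data from patients with ≥1 AEs" could suggest 8/8 = 100% where 8/40 = 20% is meant. The natural meaning is that patients, not events, are counted. The sentence states no denominator, and the statistical section includes all randomised patients. This needs a clearer sentence and no more.

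**Conclusion.** The point holds in a limited form. By making relatedness a condition of entry, without naming who judges it, by what criteria or whether blind to arm, the protocol allows doubtful or unexpected non-serious events to go unrecorded. It thereby gives up, beyond recovery, the randomised all-cause comparison of such events.

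The size is unknown, because the rates and kept fractions above are assumed. They show the direction and possible scale of the distortion, not its likely value. The primary and secondary outcomes and the sample size do not depend on this rule. It should be fixed, because safety is a stated objective and the loss is permanent, but it does not undermine the trial as a whole.

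**What to change.** In Safety Monitoring:

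1. Delete the restriction to related events and the sentence that other events are neglected.
2. Record all adverse events in both arms throughout the study, using the visits and telephone reports already planned.
3. Have the blinded outcome assessor code seriousness, severity and relatedness, with stated criteria, as variables and not as entry conditions.
4. Report all events and related events by arm, each as patients with at least one event out of all patients in that arm. This also settles the wording of the rate sentence.

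The cost is protocol and case report form wording, plus some extra entries for 80 patients, many of them unrelated minor events such as colds. If any patients have already been followed under the present rule, the report should say that their non-serious events were recorded only when judged related.

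### Sending adverse event reports to the blinded outcome assessor can reveal allocation for some electroacupuncture participants

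*Protocol*

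**What the plan says.** The Study design section of the protocol makes the blinding claim: "In this study, participants, outcome assessors and statisticians are blinded to treatment allocation".

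The Safety Monitoring section then names the contact for adverse events (AEs): "Participants were instructed to report AEs throughout the study by contacting the outcome assessor at each visit or by telephone". The treatment-related events to be recorded include "local pain from needling, slight bleeding or hematoma, persistent pain after EA, discomfort after EA", and the list ends with "stuck needle, fainting during acupuncture, broken needle, and infection". Non-serious events are kept only if they are related to EA; common events plainly unrelated to acupuncture are left out.

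The two interventions differ in penetration. The EA group section has needles inserted "to a depth of 50 to 60 mm using acupuncture needles of size 0.30×75 mm". The sham EA group section has them applied "with blunt needle tips piercing adhesive pads and not piercing the surface of the skin, using placebo needles of size 0.30×25 mm".

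**The concern.** One role is declared blind and is also the recipient of information that can identify the arm. A participant who telephones about a hematoma at a needle site tells the assessor that a needle probably went through her skin, and in this trial that happens by design only in the EA group.

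Two things are at stake. The first is efficacy. An assessor who knows some allocations may, without intending to, instruct, run or follow up an assessment differently. The disclosure is one-sided: such events can expose EA participants but not sham participants. The second is safety, which is part of the stated objective. Whether a non-serious event is recorded depends on a judgement of relatedness. If the person who takes the report makes that judgement, the content of the report may already have suggested the arm.

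**Working it through.** The question is mainly one of reading sections together. The arithmetic only gives a sense of scale.

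**Step 1. Role and information flow.** Study design blinds outcome assessors. Safety Monitoring makes the outcome assessor the contact for AE reports, at visits and by telephone, throughout the study. The protocol names no separate safety contact, sets no order in which outcomes and AEs are taken, and places no limit on what the assessor sees.

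**Step 2. Which listed events point to an arm.** This is an inference from the needle descriptions; the protocol does not state it.

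| Event | Informative about arm? |
|---|---|
| Bleeding or hematoma | Yes; in practice needs penetration |
| Stuck needle | Yes, but it happens in front of the acupuncturist, so it reaches the assessor only if the participant reports it |
| Infection | Not clearly; the list does not restrict it to the needle site |
| Broken needle | Not clearly; nothing rules out breakage of a placebo needle |
| Pain, discomfort, fainting | Possible in either arm |

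**Step 3. Timing.** Treatment is 3 sessions a week for 6 weeks, so 3 × 6 = 18 sessions, all before the week-6 outcome. Reports from this period precede the week-6 pad test and the assessments at weeks 18 and 30.

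**Step 4. How many participants.** The protocol gives no AE rates, so the rate p of EA participants reporting a penetration event is an assumption. With 40 EA participants, the chance of at least one such report is 1 − (1 − p)^40 and the expected number is 40p.

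| Assumed p | Chance of at least one | Expected number |
|---|---|---|
| 1% | 33% | 0.4 |
| 2% | 55% | 0.8 |
| 5% | 87% | 2 |
| 10% | 99% | 4 |
| 15% | over 99% | 6 |

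**Step 5. How far the primary comparison could move.** The yardstick is the design difference of 1.46 g (SD 1.74) from the sample size section. That calculation reproduces: 2 × (1.960 + 1.282)² × 1.74² / 1.46² = 29.9, so 30 per group, and 30 × 1.2 = 36 as stated. (Dividing by 0.8 gives 38; the planned 40 covers either.)

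Suppose k exposed EA participants each have a pad-test result biased by b grams in the same direction, with the sham group unaffected. The mean difference then shifts by (k/40) × b. The values of b are assumptions.

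| k | b = 0.5 g | b = 1 g |
|---|---|---|
| 2 | 0.025 g (1.7% of 1.46 g) | 0.05 g (3.4%) |
| 4 | 0.05 g (3.4%) | 0.10 g (6.8%) |
| 6 | 0.075 g (5.1%) | 0.15 g (10.3%) |

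These figures also assume that the assessor runs the week-6 pad test, which the protocol does not say.

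**The case against.** The strongest reply is that the two sections are compatible. Allocation is withheld from the assessor, and naming the assessor as AE contact does not hand it over. That is right as far as it goes. A reader might infer that the sections contradict each other, or that assessor blinding is not delivered at all. The text does not support either reading. It supports a leak that opens when a particular kind of event is reported. Even at 2 to 6 exposures, 34 to 38 of the 40 EA allocations and all 40 sham allocations remain undisclosed by this route.

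A second reply is that the link to outcomes is not documented. A reader might take it as given that the outcome assessor runs the week-6 pad test and collects the diaries and questionnaires. The protocol does not say so; the only staff it names for these measures are research assistants, at baseline. The inference is natural, but it remains an inference.

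A third is that the outcomes leave little room for assessor influence. The primary outcome is a weight. The secondary outcomes come from a participant's diary, questionnaire and self-evaluation, and reporting an AE to the assessor does not in itself tell the participant her arm. This also stands, and it limits the likely bias. It does not cover the conduct of the pad test or the eliciting and attributing of AEs, where knowledge of the arm can still matter.

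What survives all three is that the protocol fixes a reporting route that can expose the arm to a person it calls blind, and states nothing to prevent it.

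**Conclusion.** The point holds in limited form. Followed as written, the plan can unblind the outcome assessor for those EA participants who report bleeding, hematoma or a stuck needle, before the week-6 and later assessments. It can also influence the relatedness judgement on which AE recording depends; the protocol does not say who makes that judgement.

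The size is probably modest. At assumed reporting rates of 5% to 15%, 2 to 6 of 40 EA allocations are exposed. With assumed shifts of 0.5 to 1 g in each exposed result, the primary difference moves by 0.025 to 0.15 g, at most about a tenth of the design difference. The conclusion rests on these assumed rates and shifts, on bleeding and stuck needles needing penetration, and on the assessor knowing how the sham needle works.

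It is tempting to treat every listed event as exclusive to real needles and to call the defect critical. Infection and broken needle do not clearly discriminate, and no effect on the primary result has been shown. The grade is should-fix: a weakness in procedure that is easily removed and that leaves the sample size and the choice of outcomes untouched.

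**What to change.** Amend Safety Monitoring so that an existing research assistant with no part in outcome assessment takes and records AE reports, both at visits and by telephone. State that outcome assessors do not see AE information on a participant until all her outcomes through week 30 are complete. State also who judges relatedness, and name who administers the week-6 pad test.

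The treating acupuncturist should not be the contact. That person knows the allocation and would be eliciting and attributing events from their own procedure, which could bias the safety comparison. The protocol also describes no contact with the acupuncturist during the 24 weeks of follow-up.

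If the roles cannot be separated, require outcomes at each visit to be recorded before AEs are asked about. This is weaker: it protects that visit's assessment only, and a report made by telephone or at an earlier visit would still precede later assessments.

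The cost is a changed contact and form route, and a second contact point for participants. No extra staff, participants or measurements are needed.

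### Needling pain is listed as an adverse event but excluded if it remits within 30 minutes, and the VAS is conditioned on pain being present, so the arm difference in needle pain may be understated

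*Protocol*

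**What the plan says.** All the safety rules at issue are in the protocol, Safety Monitoring. Besides serious events, it limits recording to treatment-related ones: "the AEs related with EA, including local pain from needling, slight bleeding or hematoma, persistent pain after EA". The list continues with "discomfort after EA (remaining uncomfortable needle sensation, fatigue, etc), stuck needle, fainting during acupuncture, broken needle, and infection".

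Two further sentences govern pain:

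- On AE status: "Acupuncture pain with a spontaneously remission within 30 min after acupuncture was not regarded as AE". No arm is named, so the rule covers both.
- On severity: "Pain or discomfort caused by acupuncture (if there was) was assessed using a 10-point visual analogue scale", where "0 indicates no pain/discomfort, and 10 indicates the severest pain/discomfort". This sentence sets no duration limit and is not tied to AE status.

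The rate is counted per woman: "The rate of AEs were calculated using data from patients with ≥1 AEs".

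The two arms differ in what could cause pain. Under EA group, needles go 50–60 mm deep and carry a current of 1–5 mA. Under sham EA group, needling is done "with blunt needle tips piercing adhesive pads and not piercing the surface of the skin".

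**The concern.** The list gives pain from needling its own place, without qualification, alongside a separate category for lasting pain. The 30-minute rule then withdraws AE status from needling pain that settles quickly. The protocol does not say where needling pain that outlasts 30 minutes ends and the lasting-pain category begins, so two assessors could code the same event differently.

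Severity plays no part, although a severity scale is collected. Pain scored 9 that is gone at 25 minutes is not an AE; pain scored 1 that lasts 35 minutes is.

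The VAS could fill this gap, but its wording makes the score conditional on pain or discomfort having occurred. Taken literally, pain-free women have no score. A summary of the remaining scores would compare subsets defined by what happened after treatment began.

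The wording is the same for both arms, but only one arm is penetrated. Brief pain is a direct effect of penetration, so leaving it out of the AE rate can shrink a real difference. Safety is part of the stated objective. These are also rules for collecting data: an analysis plan cannot recover with certainty zeros that were never recorded.

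**Working it through.** **Figures in the plan.** The protocol gives no rate of needle pain, no share that remits within 30 minutes and no expected VAS. Its one computed figure, 36 per group for the primary outcome, reproduces as 30 × 1.2 = 36 and has no bearing here. The only inputs taken from it are 40 women per group (Sample Size and Statistical Analysis) and the 30-minute rule. Everything else below is assumed, for illustration.

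**Step 1. What the rule removes.** Let p₁ and p₀ be the proportions of EA and sham women with any needling pain. Let f₁ and f₀ be the shares of those women whose pain always remits within 30 minutes. The difference in any pain is p₁ − p₀. The difference in pain AEs is p₁(1 − f₁) − p₀(1 − f₀). The rule therefore removes p₁f₁ − p₀f₀, and it understates the difference whenever more EA than sham women have only brief pain. With a common share f, the difference becomes (1 − f)(p₁ − p₀): it shrinks by exactly f, while the expected ratio p₁/p₀ is unchanged.

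**Step 2. Range.** Expected numbers of women with a pain AE, EA versus sham, are 40 × p × (1 − f), rounded, with a two-sided Fisher exact p-value:

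| Assumed any pain, EA / sham | f = 0 (all pain counted) | f = 50% | f = 80% | f = 90% |
|---|---|---|---|---|
| 30% / 5% | 12 v 2 (p = 0.006) | 6 v 1 (p = 0.11) | 2 v 0 (p = 0.49) | 1 v 0 (p = 1.0) |
| 50% / 10% | 20 v 4 (p = 0.0002) | 10 v 2 (p = 0.025) | 4 v 1 (p = 0.36) | 2 v 0 (p = 0.49) |
| 70% / 20% | 28 v 8 (p < 0.0001) | 14 v 4 (p = 0.015) | 6 v 2 (p = 0.26) | 3 v 1 (p = 0.62) |

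In the middle row the excess of 16 women falls to 8 at f = 50% and to 3 at f = 80%.

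**Step 3. VAS.** Assume a mean of 3 among women with pain in both arms. Restricted to those women, the difference is 3 − 3 = 0. Over all women, with 0 for none, it is 3 × (p₁ − p₀):

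- 3 × (0.30 − 0.05) = 0.75
- 3 × (0.50 − 0.10) = 1.2
- 3 × (0.70 − 0.20) = 1.5

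This shows what an affected-only summary would miss. It does not show what the plan will report, because the protocol defines no VAS summary.

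**The case against.** The strongest reply is that the 30-minute rule decides only what is called an AE, not what is captured. The VAS sentence has no duration limit, so intense but brief pain can still be scored. The rule is prespecified, identical for both arms, and a defensible threshold for brief procedural pain in a treatment that deliberately seeks a needle sensation. Bleeding or hematoma, lasting pain, discomfort, fainting, stuck or broken needles, infection and all serious events remain countable. The condition attached to the VAS may mean only that pain might not occur, and the zero anchor allows pain-free women to be scored. The protocol calls for all randomised patients to be analysed, and details of the VAS summary may be in an analysis plan that is not shown.

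Most of this stands, and it rules out three stronger readings that a reader might infer:

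- *That the burden of penetrating needles is largely removed from the safety comparison.* This would need most needling pain to be brief, which the protocol does not say, and other needle-related events still count.
- *That the plan specifies a VAS comparison among affected women only.* It specifies no VAS comparison. Even an affected-only table would reveal unequal numbers if it gave them.
- *That the 30-minute rule must be deleted.* Where to set an AE threshold is a matter of judgement.

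The reply does not remove the unqualified listing followed by the exclusion, the undefined boundary with lasting pain, or the doubt over who is scored on the VAS. A VAS score for brief pain shows the arm difference only if it is tabulated by arm over a known denominator.

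**Conclusion.** The point holds as a modest, inexpensive improvement to the safety data. The AE list and the 30-minute rule do not fit together as written, and the VAS wording leaves its scored population unclear. Because only EA needles penetrate, the AE rate may understate the absolute arm difference in needle pain. If the brief share is the same in both arms, the understatement equals that share: half at 50%, about four fifths at 80%. If brief pain is rare, the effect is negligible. The pain rates, the brief share and the VAS mean of 3 are all assumptions, so no single size can be attributed to this trial. The primary and secondary outcomes are unaffected.

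**What to change.** In Safety Monitoring:

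1. Reconcile the AE list with the 30-minute rule, and state how needling pain that outlasts 30 minutes is distinguished from the lasting-pain category. The AE definition can stay if the investigators want it.
2. Report needling pain that remits within 30 minutes as a separate row by arm, with all treated women as the denominator, outside the AE rate if preferred.
3. Remove the condition from the VAS sentence. Record a score for every treated woman in both arms, with 0 for none, and summarise it over all treated women.

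The cost is a few lines of protocol text, one more table row and one VAS mark for women who would otherwise be skipped. No new instrument is needed. The downside is that the reported pain rate in the EA arm is likely to be higher.
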